**Methods:**

Sixty consenting participants with confirmed habit of tobacco smoking will be recruited and randomized into three arms to receive either auricular acupressure at five true acupoints (NADA protocol), auricular acupressure at five sham points, or no auricular acupressure at all. Participants having auricular acupressure will exert firm pressure to each acupoint bilaterally via the bead in the attached plasters whenever they feel the urge to smoke. The treatment phase will last for six weeks during which all participants will be assessed weekly to review their smoking log, state of abstinence, end-exhalation carbon monoxide levels and possible adverse effects including withdrawal reactions and stress levels. At any time, a successful quit date will be defined with continuous abstinence for the following consecutive 7 days. From then on, participants will be evaluated individually for continuous abstinence rate (CAR), end-exhalation carbon monoxide levels and adverse effects of stress and withdrawal at specified intervals up to 26 weeks. Expectancy of treatment will be assessed with a four-item Borkovec and Nau self-assessment credibility scale during and after intervention.

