### Sample size calculation and randomisation

A convenience sample size of a total of 60 participants will be recruited, with 20 participants per arm after randomisation. Compared to other pilot studies, this sample size is deemed sufficient and appropriate statistical methods will be adopted to accommodate for foreseeable limitations during final analysis (see section on statistical analysis). Randomisation and allocation of subjects will be performed according to the CONSORT standards in terms of randomisation type[37], randomisation generation[38], allocation concealment[39]. All participants will be informed that they will be randomly allocated to one of the three study arms using a computer generated sequence created by the SPSS 11.0 (IBM^© ^SPSS^© ^Statistics, NY, USA). The random allocation will only be disclosed on the date of treatment commencement. Apart from Arm 3 (passive controls with no acupressure), blinding will be ensured in participants of Arm 1 (true acupuncture points) and Arm 2 (sham points). In particular, participants receiving acupressure will be told that the actual points chosen may vary over time to eliminate guessing amongst them during the study. Efforts will also be made to avoid contacts between all participants.

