### Verum acupressure (arm 1)

Participants in Arm 1 will receive a 2 mm × 2 mm acupressure plaster (each with a single *Melastoma candidum *seed, see Figure 3a and 3b) at each of the 5 auricular acupoints bilaterally (Lung 2, Shen Men, Autonomic Point, Liver and C. Kidney) according to the NADA protocol (Figure 1). Participants will be instructed to exert firm digital pressure to each acupoint for five seconds via the central plastered seeds whenever they feel the urge to smoke. The seeded plasters are water resistant and should remain in position until the next weekly scheduled review, when they will be replaced with new ones. If the plasters detach, the participants will return to the research center for replacement without delay. Period of intervention will be six weeks (week 2 to week 7).

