### Outcome measures

The primary outcome measures in our study will be 7-day point prevalent abstinence rate (PAR), continuous abstinence rate (CAR), end-expiratory carbon monoxide levels (CO), nicotine withdrawal symptoms according to the Minnesota Nicotine Withdrawal Scale (MNWS) and stress level according to the Stress Check List (SCL). PAR is defined as abstinence from tobacco smoking for the previous 7 days, whereas CAR is defined as abstinence since the target quit date. The time taken (T) to reach the quit date is also recorded. During the active intervention period (week 2 to week 7), the following will be assessed weekly: number of cigarettes smokes per day, CO, MNWS and SCL. At week 3, 5 and 7, CAR and PAR will be assessed. At week 13 and week 26, successful quitters will be assessed for CO, PAR, SCL and MNWS. At week 2 and week 8/one week after successful quitting, expectancy of treatment will be assessed in all participants with a modified 4-item Borkovec and Nau self-assessment credibility scale as adopted by Tough *et al. *[40] in acupuncture related studies.

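### Continuous abstinence (CAR), a primary outcome, is given two incompatible start dates and two conflicting assessment schedules

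*Protocol article*

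**What the plan says.** Outcome measures names CAR among the primary outcomes and states that "CAR is defined as abstinence since the target quit date". The next sentence reads: "The time taken (T) to reach the quit date is also recorded". The assessment times follow: "At week 3, 5 and 7, CAR and PAR will be assessed", and for later follow-up "At week 13 and week 26, successful quitters will be assessed for CO, PAR, SCL and MNWS". CAR is absent from that second list.

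The Methods paragraph of the Abstract uses a different date: "At any time, a successful quit date will be defined with continuous abstinence for the following consecutive 7 days". It continues "From then on, participants will be evaluated individually for continuous abstinence rate (CAR"), along with carbon monoxide and adverse effects, at intervals that extend to 26 weeks.

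Verum acupressure (arm 1) gives the treatment window: "Period of intervention will be six weeks (week 2 to week 7"). Sample size calculation and randomisation gives the numbers: "A convenience sample size of a total of 60 participants will be recruited, with 20 participants per arm after randomisation". Statistical analysis compares CAR, like the other outcomes, between each pair of arms.

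**The concern.** A target quit date is fixed in advance, and anyone can be scored against it whether or not they stop smoking. An achieved quit date exists only for those who stop, and it is known only afterwards. The article uses both for the same primary outcome and says nowhere who sets the target date or when. Two analysts with the same smoking logs could therefore report different CARs and each cite the protocol.

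This matters for what the pilot is meant to deliver. Background says its purpose is to supply the effect size and sample size for later trials, and it criticises earlier acupressure studies for not defining successful abstinence uniformly. A CAR with no settled start, and no listed assessment beyond week 7, cannot serve as a reproducible planning figure.

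**Working it through.** The only related figure in the article is the sample size, 3 × 20 = 60. It agrees arithmetically, but it is a convenience sample and nothing in it depends on CAR. The check is therefore a comparison of the texts, followed by simple arithmetic.

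**1. Start of the clock**

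| Source | Start date | Exists for everyone? |
|---|---|---|
| Outcome measures, CAR definition | target quit date | would, if set; no section sets it |
| Outcome measures, time T | a date that is reached | no |
| Abstract, Methods | date followed by 7 abstinent days, at any time | no |

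The recorded time T fits an achieved date and not a planned one, so Outcome measures is not consistent even within itself.

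**2. Schedule**

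| Source | When CAR is assessed |
|---|---|
| Abstract, Methods | individually from the quit date, up to 26 weeks |
| Outcome measures | study weeks 3, 5 and 7; not listed at weeks 13 and 26 |

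The article does not say whether the 26 weeks count from study start or from each quit date. If they count from the quit date, a week-2 quitter finishes at study week 2 + 26 = 28 and a week-7 quitter at 7 + 26 = 33. Both fall after the last contact that Outcome measures lists.

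**3. Abstinence required, if CAR is counted from individual quit dates but read at study weeks**

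Weeks required = assessment week − quit week. The 7-day rule confirms the date one week after the quit week.

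| Quit week | By week 7 | By week 13 | By week 26 | Confirmed in week |
|---|---|---|---|---|
| 2 | 5 | 11 | 24 | 3 |
| 3 | 4 | 10 | 23 | 4 |
| 4 | 3 | 9 | 22 | 5 |
| 5 | 2 | 8 | 21 | 6 |
| 6 | 1 | 7 | 20 | 7 |
| 7 | 0 | 6 | 19 | 8 |

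The spread at week 26 is 24 − 19 = 5 weeks, and 5/24 = 21%. A quit date in week 7 is confirmed only in week 8, after the last CAR assessment listed.

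For scale, assume a constant weekly relapse probability h after the guaranteed first week, so that CAR at week 26 = (1 − h)^(26 − quit week − 1). The values of h are assumptions; the article gives none.

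| h | Week-2 quit (23 weeks at risk) | Week-7 quit (18 weeks at risk) |
|---|---|---|
| 3% | 49.6% | 57.8% |
| 5% | 30.7% | 39.7% |
| 8% | 14.7% | 22.3% |

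**4. Denominator**

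With q quitters among 20 and s of them still abstinent, CAR is s/q among quitters and s/20 among all randomised. The two differ by a factor of 20/q. The counts below are assumed.

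| q | s | Of quitters | Of randomised | 20/q |
|---|---|---|---|---|
| 10 | 4 | 40% | 20% | 2 |
| 4 | 2 | 50% | 10% | 5 |

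With these counts the order of the two arms reverses between denominators.

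**The case against.** The strongest reply is that this is loose wording in a condensed article. One could take the word target as a slip, read the achieved date throughout, and leave the denominator to the full protocol or analysis plan. An individual clock from the quit date is a legitimate design choice. The study is also a pilot with a convenience sample, and CAR is one of five primary measures.

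Part of this stands, and it rules out several stronger readings that a reader might infer:

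- *That CAR has no valid denominator.* The denominator is unstated, not impossible. All 20 randomised per arm, with never-quitters counted as not abstinent, is compatible with Statistical analysis. The restriction to successful quitters applies to weeks 13 and 26, where CAR is not listed, so the text does not prescribe a quitters-only CAR.
- *That the quit date is assigned after 7 days already abstained.* The Abstract puts the date first; the 7 days follow and confirm it.
- *That the plan favours an arm that quits later.* Follow-up of equal length from each quit date gives equal time at risk, and Outcome measures has no week-26 CAR to distort. The 24-versus-19-week spread needs the Abstract's clock on the calendar of Outcome measures.
- *That CAR merely repeats 7-day point prevalence (PAR).* Someone who quits in week 3, smokes in week 5 and is abstinent throughout week 7 succeeds on PAR and fails on CAR counted from week 3. The two nearly coincide only if the quit date resets after relapse, which the article does not say.

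The reply does not remove the contradiction itself. Both start dates and both schedules are printed and disagree, so this is more than detail left to another document.

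**Conclusion.** The point holds as a contradiction in the definition and timing of a primary outcome. As printed, CAR is counted both from a target date that is never set and from an achieved date that never-quitters lack and that varies between quitters. It is both carried to 26 weeks and missing from the week-13 and week-26 assessments. These conclusions rest on the text alone. Figure 2, the study flow chart, was not available to this review.

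The size is conditional. A 5-week (21%) spread in required abstinence at week 26 arises only if the two schedules are combined. The relapse percentages depend on assumed weekly rates of 3% to 8%, and the reversal between arms on assumed counts. They show what an unsettled definition could do; they do not show that the plan is biased towards any arm. The other four primary measures do not use the CAR origin.

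**What to change.** Reconcile the Abstract with Outcome measures before any comparison of CAR between arms:

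1. State one time origin, the same in all arms, that also serves the assessments at weeks 3, 5 and 7. Examples are a prespecified target date or a fixed study week with a stated grace period. An origin at the end of the intervention would leave CAR undefined at those three visits. State whether a relapse can reset the date.
2. Name all 20 randomised per arm as the denominator, with never-quitters counted as not continuously abstinent.
3. Add CAR to the week-13 and week-26 list, with a question on any smoking since the origin; the listed 7-day PAR does not cover the whole interval. State whether weeks 13 and 26 count from study start.
4. Keep T as a separate time-to-event outcome, with those who never reach a quit date censored.

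The cost is revised wording and one added question at existing contacts, with no new visits. Reported CAR may rise or fall, depending on the origin chosen: a later origin forgives earlier relapses and shortens the abstinence required, while the all-randomised denominator lowers the rate relative to a quitters-only figure.

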### Methods of smoking cessation

Various methods of smoking cessation are available and can be broadly divided into pharmacological and non-pharmacological methods, which often work better in combination[6]. Nicotine replacement therapy is one of the commonest prescribed treatments which enhances the overall rate of quitting by 50-70%[7] with a stand-alone success rate of 6-20%[8-10]. Newer oral medications include sustained-release bupropion[11] and varenicline[12], which significantly improve smoking abstinence with a higher success rate of 30-50%[11-14]. Thus said, the quote success rates may vary according to the length of continuous abstinence which can range from 3 months to 2 years.

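### The abstract follows continuous abstinence to 26 weeks, but the visit schedule lists it only at weeks 3, 5 and 7; the two must be reconciled

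*Protocol article*

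**What the plan says.** The Outcome measures section of the protocol article names five primary outcomes: PAR, CAR, CO, the withdrawal score (MNWS) and the stress score (SCL). It keeps the two abstinence measures apart: "PAR is defined as abstinence from tobacco smoking for the previous 7 days, whereas CAR is defined as abstinence since the target quit date".

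The article then gives two accounts of when CAR is measured.

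- **Abstract, Methods.** Once a successful quit date is reached, each participant has CAR, CO, stress and withdrawal assessed "at specified intervals up to 26 weeks". PAR is not mentioned there.
- **Outcome measures.** "At week 3, 5 and 7, CAR and PAR will be assessed". For the later visits: "At week 13 and week 26, successful quitters will be assessed for CO, PAR, SCL and MNWS". CAR is not mentioned there.

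The Statistical analysis section includes CAR among the outcomes compared between each pair of arms. It names no time point, so it does not settle which account applies.

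**The concern.** Two explicit statements about a primary outcome disagree. The abstract follows quitters with CAR and leaves out PAR; the schedule follows them with PAR and leaves out CAR. Staff who work from the Outcome measures list would not record CAR after week 7, although the abstract promises it to 26 weeks.

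At stake is the difference between having stayed off cigarettes since quitting and having been off them for the past week. The Background says the pilot is meant to supply the sample and effect size for later trials, and it faults earlier acupressure studies for using differing definitions of successful abstinence. If the late visits record only a 7-day measure, the pilot has no 13-week or 26-week result for sustained abstinence. The gap is hard to repair once the visits have passed, because the abstract describes review of the smoking log only for the six-week treatment phase.

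**Working it through.** The plan states no figure on this point, so there is none to reproduce. The check sets the two accounts side by side and then counts the weeks that each late measure covers.

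**Side by side**

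| Time | Abstract | Outcome measures |
|---|---|---|
| Weeks 3, 5, 7 | CAR from the quit date, intervals not named | CAR and PAR |
| Weeks 13, 26 | CAR, within the 26-week horizon | CO, PAR, SCL, MNWS |

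PAR cannot be shorthand for CAR in the last row, because the same section defines them separately and lists both at weeks 3, 5 and 7.

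**Coverage if the Outcome measures list is followed as written**

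Inputs, all from the Outcome measures section: last listed CAR assessment at week 7, later visits at weeks 13 and 26, PAR look-back of 7 days (1 week).

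1. Time after the last listed CAR assessment: 26 − 7 = 19 weeks.
2. Time covered by the two PAR windows: 2 × 1 = 2 weeks.
3. Time with no listed abstinence measure: 19 − 2 = 17 weeks, and 17/19 is about 89%.
4. These 17 weeks lie in two stretches: (13 − 7) − 1 = 5 weeks before the week 13 window, and (26 − 13) − 1 = 12 weeks before the week 26 window.

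The article gives no detection window for CO. I take it to reflect smoking around the visit, so that it does not widen the coverage.

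**What is seen and what is missed**

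- A quitter who smokes in the 7 days before week 13 or week 26 is not abstinent by PAR at that visit, and CO is there as a check. This relapse is seen.
- A quitter who starts again in week 9 and smokes through week 24 is also seen, at week 13.
- A quitter who stops in week 4, smokes in weeks 14 to 24 (24 − 14 + 1 = 11 weeks) and stops in week 25 before the 7-day window opens is abstinent by PAR at both visits. This relapse is missed.

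For someone who quit by week 7, the listed data therefore give only an upper bound. Those abstinent by CAR at week 7 and by PAR at weeks 13 and 26 include everyone continuously abstinent to week 26, and also anyone who smoked only inside the two gaps.

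**The case against.** The strongest reply is that one term has simply dropped out of a list. The abstract says that CAR continues, the analysis section compares CAR with no cut-off at week 7, and nothing in the article says that it stops. The article is a condensed account, its flow chart is not shown, and it does not give the questions asked at follow-up. This stands to the following extent: a reader might infer that the trial measures continuous abstinence only to week 7, and the document does not establish that, because it says both things. Condensation does not remove the conflict, since both statements are explicit.

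A reader might also infer that late relapse goes undetected. That is not so. PAR and CO at weeks 13 and 26 detect relapse present at those visits, and only smoking confined to the gaps escapes.

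A third tempting step is to hold the pilot to the Background remark that "the quote success rates may vary according to the length of continuous abstinence which can range from 3 months to 2 years". That sentence describes success rates quoted in the literature. It sets no benchmark for this trial, so the pilot cannot be said to fall short of one.

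Finally, this is a pilot in a convenience sample of 60, aimed at safety, feasibility and planning. That limits the consequences, and PAR with CO at 13 and 26 weeks remains useful for planning. But CAR is a stated primary outcome, and the pilot is meant to inform later effect sizes, so the schedule for it should be unambiguous.

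**Conclusion.** The point holds as a contradiction on a primary outcome: CAR to 26 weeks in the abstract, CAR listed only at weeks 3, 5 and 7 in Outcome measures, and no CAR time point in the analysis section to decide between them.

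Its consequence is conditional. If the Outcome measures list is followed, 17 of the 19 weeks after week 7 have no listed abstinence measure, and sustained abstinence at 13 and 26 weeks cannot be told apart from point abstinence. If the abstract is followed, this gap does not arise. The count assumes that weeks 13 and 26 are study weeks, in the same numbering as weeks 2 to 7, and that the late visits ask only what the list names. How many participants would be misclassified cannot be derived, because the article gives no relapse rates.

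**What to change.** In Outcome measures, add CAR to the week 13 and week 26 assessments, so that the schedule agrees with the abstract. Collect it by asking at each of these visits about any smoking since the quit date, not only in the last 7 days. Report 26-week CAR beside 7-day PAR. Make the change before the week 13 visits begin.

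The cost is one sentence in the schedule and one extra question at two visits that already take place. The 26-week CAR can be no higher than the 26-week PAR on the same denominator, because anyone abstinent since a quit date at least 7 days earlier is also abstinent for the last 7 days. The sustained figure may therefore look less favourable.

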### Co-existent treatment

A record of co-existent treatments, both pharmacological and non-pharmacological, will be recorded for every participant. Any treatment pertaining to smoking cessation should be discontinued at the start of the run-in week and will not be resumed until the participant completed the study or is withdrawn from the study due to treatment failure or adverse events. Equally, all participants will be advised not to attempt any smoking cessation 2 weeks before the run-in period.

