### Statistical analysis

Baseline characteristics of participants (age, number of cigarettes smoked per day, history of packed-years and number of previous cessation attempts) in all the three arms will be expressed as mean values ± standard deviation (SD). The null hypothesis will be adopted in comparing the outcomes (PAR, CAR, CO levels, MNWS score and SCL scores) between Arm 1 and Arm 3, Arm 2 and Arm 3, and finally between Arm 1 and Arm 2. In view of the small sample size for each arm, the Mann-Whitney-Wilcoxon two-sample rank sum test will be used for each Arm pair. Medians will be calculated with the quartiles and the Mann-Whitney *U*. Where possible, treatment effect for each Arm pair comparison will be expressed using the Hodges-Lehmann estimator with the 95% confidence intervals and significance levels.

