### Adverse events and withdrawal from studies

Part of the objectives of our pilot study is to assess the possible adverse effects due either to the auricular acupressure or, due to withdrawal and stress from smoking cessation. The nature and severity of the adverse effects will be recorded and assessed with the MNWS and SCL scores. At any time, participants may withdraw from the study if they develop severe nicotine withdrawal reactions or anxiety symptoms; if they have any adverse effects of pain, discomfort, inflammation or infection at the local sites of the plaster; if there is any inter-current illness that would, in the judgment of the investigators, affect outcome measures to a significant degree; and finally, as requested by the participants.

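### Weeks 13 and 26 measure CO, MNWS and SCL in quitters only, so late arm comparisons of these primary outcomes are not between randomised groups, and late PAR and CAR need an all-randomised denominator

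*Protocol article*

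**What the plan says.** Outcome measures makes five outcomes primary: "The primary outcome measures in our study will be 7-day point prevalent abstinence rate (PAR), continuous abstinence rate (CAR), end-expiratory carbon monoxide levels (CO"), together with the MNWS and SCL scores. It then sets two different assessment populations.

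- **Weeks 2 to 7.** Cigarettes per day, CO, MNWS and SCL are taken weekly, and PAR and CAR at weeks 3, 5 and 7. None of this is restricted to quitters.
- **Weeks 13 and 26.** "At week 13 and week 26, successful quitters will be assessed for CO, PAR, SCL and MNWS". No late visit is described for anyone else.

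The Methods part of the Abstract agrees. It says that "a successful quit date will be defined with continuous abstinence for the following consecutive 7 days", and continues: "From then on, participants will be evaluated individually for continuous abstinence rate (CAR), end-exhalation carbon monoxide levels and adverse effects of stress and withdrawal", at intervals up to 26 weeks. Late follow-up thus starts from an individual's own quit. CAR is missing from the week 13 and 26 list in Outcome measures, but the Abstract includes it.

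Statistical analysis plans on "comparing the outcomes (PAR, CAR, CO levels, MNWS score and SCL scores) between Arm 1 and Arm 3, Arm 2 and Arm 3", and also Arm 1 against Arm 2. It adds that "the Mann-Whitney-Wilcoxon two-sample rank sum test will be used for each Arm pair". It names no time point, analysis set or denominator, and does not exempt the late visits.

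Co-existent treatment refers in passing to a participant who "is withdrawn from the study due to treatment failure or adverse events". Adverse events and withdrawal from studies gives its own list of withdrawal reasons, and treatment failure is not among them.

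**The concern.** Randomisation makes the arms comparable at entry. It does not make those who quit in Arm 1 comparable with those who quit in Arm 3. If acupressure helps more dependent smokers to quit, the Arm 1 quitters will include people who would have kept smoking in Arm 3. Their later CO, withdrawal and stress scores are then set against those of a smaller, more strongly selected control group. A difference can appear without any effect on the score, and a real one can be hidden.

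Two stated purposes are at stake. The Background says the pilot is meant to supply the effect size and sample size for later trials, so a distorted late effect would carry forward. The adverse events section uses MNWS and SCL to judge harm, so late tolerability would be known only in those who succeeded.

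**Working it through.** **Plan's own figure.** 3 arms × 20 = 60, as stated. It is a convenience sample, so there is no power calculation to reproduce. The check concerns who is measured.

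**Inputs.** 20 per arm comes from Sample size calculation and randomisation. The Background quotes success rates of 6–20% for stand-alone nicotine replacement and about 45% for acupuncture. I borrow these only as a range, with 10% and 30% as points within it. They are rates for long abstinence, whereas a successful quit here needs 7 days, so the counts below may be too low. Week 26 retention (30–70%) and the correlations in step 3 are assumptions.

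**1. How many are seen late.** Expected number = 20 × quit rate.

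| Quit rate | Expected quitters per arm |
|---|---|
| 45% | 9 |
| 30% | 6 |
| 20% | 4 |
| 10% | 2 |
| 6% | 1.2 |

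At 10%, the chance of no quitters in an arm is 0.90^20 = 0.12, and of fewer than 4 it is 0.87.

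**2. Abstinence: quitters or all randomised as denominator.**

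- *Assumed counts.* In Arm 1, 9 of 20 quit and 5 are still abstinent; in Arm 3, 3 of 20 quit and 2 are still abstinent. Among quitters: 5/9 = 56% vs 2/3 = 67%, favouring control. Among all randomised: 5/20 = 25% vs 2/20 = 10%, favouring acupressure.
- *Assumed equal retention.* Quit rates of 45% vs 10% with 50% retention give 50% vs 50% among quitters, a difference of 0. Over all randomised they give 0.45 × 0.50 = 22.5% vs 0.10 × 0.50 = 5.0%, a difference of 17.5 points. Over retention of 30–70% and quit-rate pairs 45/10, 45/20 and 30/10, the difference runs from 0.30 × (30 − 10) = 6.0 to 0.70 × (45 − 10) = 24.5 points.

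The denominator decides the answer, but both versions can be computed from the data the plan collects.

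**3. CO, MNWS and SCL: no denominator helps.** A non-quitter has no late value, and none follows from being a non-quitter. To size the selection, let dependence correlate 0.7 with the tendency not to quit and ρ = 0.3 to 0.7 with the score, with no treatment effect on the score. For quit rate q, the mean score among quitters is −0.7 × ρ × φ(z_q)/q, where φ is the standard normal density and z_q its q-quantile.

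- φ(z_q)/q is 0.880 at 45%, 1.400 at 20% and 1.755 at 10%.
- Smallest shift (ρ = 0.3, 45% vs 20%): 0.7 × 0.3 × (1.400 − 0.880) = 0.11 SD.
- Largest shift (ρ = 0.7, 45% vs 10%): 0.7 × 0.7 × (1.755 − 0.880) = 0.43 SD.

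Simulation gave the same 0.11 and 0.43. The arm with more quitters looks worse.

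**4. What the rank-sum test can show.** The smallest exact two-sided p is 2/C(n1+n2, n1).

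| Quitters | Smallest p |
|---|---|
| 9 vs 1 | 2/10 = 0.20 |
| 3 vs 3 | 2/20 = 0.10 |
| 6 vs 2 | 2/28 = 0.071 |
| 3 vs 4 | 2/35 = 0.057 |
| 9 vs 2 | 2/55 = 0.036 |
| 4 vs 4 | 2/70 = 0.029 |
| 9 vs 3 | 2/220 = 0.009 |

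In the step 3 setting, the simulated rejection rate of the quitter-only test was 1.4% to 4.8% at the nominal 5% level.

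**The case against.** The strongest reply is that the text says who is visited, not who is analysed. No quitter-only denominator is stated. Someone who has never quit can be counted as not abstinent, so late PAR and CAR can be computed over all 20 per arm, and such counting rules commonly sit in an analysis plan or full protocol not shown here. That stands. It does not reach CO, MNWS and SCL, because the restriction is a stated data-collection rule and unmeasured values cannot be recovered at analysis.

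It is also fair that this is a pilot of safety and feasibility, and that all five primary outcomes have assessments in weeks 2 to 7 that are not limited to quitters. That limits the damage to the late visits.

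A reader might infer more than the documents support:

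- *That every late comparison is lost.* Not so for PAR and CAR, as above.
- *That treatment failures leave the study as a rule.* The only basis is a passing phrase in a rule on resuming other treatment, and the withdrawal section does not list it.
- *That people who quit after week 7 are never seen.* The Abstract allows a quit date at any time, and nothing closes quitter status at week 7.
- *That CO is low in all quitters.* Quitters who relapse are still assessed, and their CO need not be low.
- *That no late test could reach significance.* This holds for 3 vs 3 and 3 vs 4, but not for 4 vs 4.
- *That withdrawal for intolerance is part of the defect.* The text is permissive: "participants may withdraw from the study if they develop severe nicotine withdrawal reactions or anxiety symptoms". Such withdrawal occurs in any trial, and handling the missing values is ordinary analysis-plan content.

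**Conclusion.** The concern holds for the late visits. Any week 13 or 26 arm comparison of CO, MNWS or SCL is conditioned on a post-randomisation result that treatment may change, and analysis cannot repair it. Late PAR and CAR are sound only with everyone randomised in the denominator, which the article does not fix.

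The harm is a biased estimate and lost power. The simulations did not show an inflated type I error. The design facts come from the text. The sizes (a sign reversal in one example, 6.0 to 24.5 points hidden, a shift of 0.11 to 0.43 SD) rest on assumed counts, quit rates, retention and correlations, and show what can happen rather than what will.

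**What to change.** - In Outcome measures, replace *successful quitters* with *all randomised participants* for weeks 13 and 26, including those who stop the plasters but still agree to follow-up.
- State that late PAR and CAR are reported over all randomised to the arm, with those not assessed counted as smoking.
- If non-quitters cannot be contacted, label late CO, MNWS and SCL as descriptive among quitters. Do not test them between arms, and do not use them for the effect size of future trials.
- Reconcile the reference to treatment failure in Co-existent treatment with the list in Adverse events and withdrawal from studies.

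The cost is a change of wording and two short contacts per non-quitter, in a trial of 60 people. Abstinence percentages will look lower. The change must be made before late follow-up starts, because the missing measurements cannot be collected afterwards.
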